### Lessons from Kids-HD

In 2009, the National Institute of Health (NIH) -funded Kids-HD study (ClinicalTrials.gov Identifier: NCT01860339) was launched at the University of Iowa, investigating the impact of *mHTT* on brain development in children at risk for HD [7]. For research purposes only, children aged 6–18 years-old at risk for HD (defined as having a parent/grandparent with HD) were genotyped and categorized as gene-expanded (i.e., GE, CAG >= 36) or gene-non-expanded (i.e., GNE, CAG < 36). The GNE children served as an excellent control group, given that being raised in an HD family can produce unique psychosocial strain not captured by children of non-HD families. A separate group of age-matched participants with no familial link to HD was also recruited as a comparison group. The Kids-HD study modeled the progression of HD several decades before the predicted age of motor onset in the GE participants. In total, we collected data from 406 individuals (13.73 ± 4.33 year; 177 Males, 227 Females; 2 unspecified) across 663 visits. Over the years, the Kids-HD study produced several key findings (Table 1). Some highlights include:

**Table 1 pone.0336088.t001:** Summary of Kids-HD papers/findings.

Clinical outcomes		
**Reference**	**Objective**	**Results/Conclusions**
Lee et al., 2018 [20]	Assess CAG effect on cognition in GE and GNE children aged 6–18 years.	*mHTT* has an inverted U-shaped effect on general intelligence (GAI): GAI scores increased and decreased with repeat length before and after 40–41 repeats, respectively, suggesting antagonistic effect of *HTT* on intelligence.
Tereshchenko et al., 2020 [21]	To determine the impact of *mHTT* on human measures of growth, including height, weight, and body mass index (BMI), between child and adolescent carriers of *mHTT* and control peers.	Decades before HD symptom onset, physical growth is abnormal in adolescent carriers of *mHTT*, suggesting that developmental aberrations may be systemic and a vital part of disease pathology.
Schultz et al., 2021 [14]	Evaluate the trajectory of cognitive skill development as a function of CAG repeat length in children and adolescents that carry the mutation that causes HD.	The development of verbal skills plateaus earlier as CAG repeat length increases.

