**Neuroimaging outcomes**		
**Reference**	**Objective**	**Results/Conclusions**
Lee et al., 2017 [13]	Evaluate CAG effect on brain structure and function in healthy controls aged 6–18 years.	CAG repeats are positively and negatively associated with brain structure changes and higher IQ in females and males, respectively.
van der Plas et al., 2019 [15]	Evaluate brain growth trajectories in child and adolescent carriers of *mHTT* compared to peers without the mutation.	GE individuals have greater striatal and pallidal volume compared with GNE, suggesting atypical brain development. CAG repeat length is positively correlated with early life striatal volume and a steeper slope of decline later in life.
Tereshchenko et al., 2020 [25]	Compare functional connectivity between the striatum and cerebellum in GE and GNE children at risk for HD.	Striatal-cerebellar resting state functional connectivity is greater in GE compared to GNE between in individuals 6–12 years old and continues to decline linearly afterwards.
Reasoner et al., 2022 [16]	Evaluate the impact of *mHTT* on the developmental trajectories of cortical thickness and surface area.	Cortical, but not striatal, volume is similar between GE and GNE individuals across age and not affected by CAG repeat length.

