***HTT* impacts brain structure and function along the entire spectrum of repeats**: Higher repeats are associated with better cognitive skill and greater brain volume in GE and GNE individuals [13,14].**Methodological challenges of modeling age and CAG separately, versus years-to-onset model (which incorporates both):** The Kids-HD study employed an accelerated longitudinal design (ALD), the gold standard for evaluating brain development in children, which combines cross-sectional and longitudinal data to model age-related changes across a broad developmental window. This model showed not only interesting findings of accelerated striatal development, where GE children reached peak striatal volume years before the GNE group, but that these trajectories were profoundly affected by CAG repeat length [15]. We also found that every CAG repeat conferred a greater advantage in general cognitive ability [14]. This effect peaked at repeats of 43 and individuals with longer CAG repeats showed trajectories that were declining in function after age 15, likely representing changes due to the degenerative phase of the disease. The age-trajectory modeling results highlighted the profound consequences *HTT* and CAG repeat-length has on neurodevelopment. These findings recapitulate the well-established negative relationship between CAG repeat length and age of motor onset and require an updated model to take both factors, and their interactions, into account. Given the influence CAG repeats and age exert on longitudinal brain development, we began modeling the data in a Years-To-Onset (YTO) fashion to evaluate the time course of the disease from development to degeneration. The YTO model predicts the age of motor onset based on the participant’s current age and CAG repeat length. Importantly, the YTO model can reveal information about disease trajectory that is obscured when plotting data by age. For example, Reasoner et al. (2022) found that cortical volumes are similar across age groups [16], while Neema et al. (2024) found evidence for higher and lower cortical volumes depending on the YTO of the individual [17]. The critical difference between approaches is that while higher age and lower YTO both predict decline in cognitive and motoric function, age-only models ignore variability in disease trajectory caused by CAG repeat length. An example of the difference between an age-only trajectory and a YTO model is as follows: An 8-year-old with a CAG repeat length of 48 and a 22-year-old with a CAG length of 43 both have 26 YTO, despite being on opposite ends of the age trajectory model. Thus, potential differences in cortical volumes could have been missed by Reasoner et al. (2022) because participants at similar ages were at different points in their disease trajectory. Additionally, when evaluating a biomarker of degeneration in Kids-HD (neurofilament light; “NfL”), we found that NfL levels are normal as far back as 40 YTO but rise around 20 YTO [18]. These findings support the notion that the YTO model can accurately characterize the developmental phase of the disease process, which occurs 20 years before the onset of motor symptoms.**The antagonistic pleiotropy theory of *HTT* and its implications for neurodevelopment:** In our most recent publication, we revealed that GE individuals from 50−20 YTO have larger cerebral volumes, more cortical surface area, and higher IQs compared to GNE subjects, but the opposite is true after 20 YTO [17]. Striatal and pallidal volumes remain comparable in volume to GNE until 20 YTO after which they dramatically decline in volume, consistent with early vulnerability of the basal nuclei. These findings challenge the traditional concept of HD as a uniquely neurodegenerative disorder and highlight the neurodevelopmental role of *mHTT.* Additionally, Kids-HD research uncovered potential early advantages of *mHTT* in GE children, such as larger brain development that supports enhanced cognitive development and reduced depression/anxiety. However, these children will indeed develop HD, highlighting the yoking of advantage with disadvantage. Our findings support the notion of antagonistic pleiotropy in HD, where the same neurodevelopmental differences that confer early advantage eventually lead to vulnerability and subsequent degeneration [19]. Collectively, they reshape our understanding of the evolutionary implications of *mHTT* and its potential role in brain development

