### Study period and recruitment goals

ChANGE-HD was originally planned as a 5-year study, aiming to complete 1,500 assessments of 400 participants by the end of the fifth year. However, the COVID-19 pandemic delayed study progress by causing significant disruptions in recruitment and scheduling across the five original study sites and required us to update our timelines after Year 2 (Table 3). As a result, the assessment period, including pre-COVID data collection, was extended to approximately seven years and our recruitment targets were changed to 450 participants across 1,030 assessments. Note that the extension allowed for the inclusion of new baseline visits, as well as additional repeat visits for those already enrolled. Actual recruitment values by site and year are shown in Table 4. Despite the disruptions of COVID-19, our most recent power analysis shows that we are still on track to achieve our study aims (see *Power analysis and sample size calculation*).

**Table 3 pone.0336088.t003:** Study timeline and recruitment targets. Numbers represent the targeted number of subjects and assessments, respectively.

	Year 1 ‘19‐20	Year 2 ’20‐21	Year 3 ’21‐22	Year 4 ’22‐23	Year 5 ’23‐24	Year 6 ’24‐25	Year 7 ’25‐26	Cumulative Total Target
**Target Total**	50/200	80/300	110/400	110/400	50/200			400/1500
**Revised Target after Year 1**		80/300	107/400	107/400	106/400			400/1500
**Revised Target after Year 2**		30/100	80/300	110/400	100/400	80/300		400/1500
**Revised Target after Year 3**		30/100	80/200	100/200	100/200	100/200	40/130	450/1030

**Table 4 pone.0336088.t004:** Recruitment by Site and Year. * - As of 02/20/2026.

	2020	2021	2022	2023	2024	2025	2026*	Total Recruitment
**The University of Iowa**	28	43	36	49	62	77	7	**302**
**CHOP**	3	10	27	40	44	55	8	**187**
**Columbia University**	7	16	26	19	27	24	0	**119**
**UT Houston**	0	13	36	38	30	36	0	**153**
**UC, Davis**	9	4	22	26	33	18	0	**112**
**Vanderbilt University**	0	0	0	0	63	63	5	**131**
**Cumulative Total**	**47**	**133**	**280**	**452**	**711**	**984**	**1004**	**1004**

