### Participants

At baseline, approximately 450 total participants will be enrolled across all sites. Although annual visits are not required for an ALD design, retention is best with close follow-up, and subjects are asked to return annually. We aim to recruit an even distribution of subjects across age groups, with 225 participants in the range of 6–18 years-old and the remaining participants in the range of 19–30 years-old.

Inclusion criteria:

Between 6–30 years oldFluent in EnglishHave a biological parent or grandparent who has been genetically or clinically diagnosed with HD, indicating that the participant is at risk for HD (determined from participant or family report)Demonstrate an age-appropriate understanding of HD and its risks (If the parents indicate that their child is unaware, we will not enroll the participant until an age-appropriate discussion has occurred)

Exclusion criteria:

A history of medical diagnoses that could potentially confound the study results (e.g., major head trauma, seizures, tumors, or any other major medical illness requiring ongoing care). If an aspect of their medical history obscures their symptoms as being directly attributable to HD (e.g., a concomitant congenital disorder) they are excluded from participation.Have Juvenile-onset HD (JOHD)MRI contraindications. Participants of childbearing potential must undergo a urine pregnancy test before their MRI. If positive, they are excluded from the MRI but may still complete other assessments.Manifestation of overt motor features of HD. This is ascertained by reporting from parents (or participants themselves if they are over 18) during a screening visit. If the participant or the parent reports that they are currently manifesting any motor symptom of HD, the participant is referred to a child or adult neurologist for clinical evaluation. These individuals are also invited to participate in the JOHD study if they were diagnosed with JOHD before the age of 21 (see below).

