$$\begin{array}{c} Age\;of\;motor\;symptom\;onset=\text{2}\text{1}.\text{5}\text{4}-(\text{9}.\text{5}\text{5}\text{6}-\text{0}.\text{1}\text{4}\text{6}*CAG) \end{array}$$

YTO is then calculated by simply subtracting participants’ ages (in years) from age of motor symptom onset. (The abbreviation YTO, now established by precedent, stands for a slight misnomer. The value is the number of years from the mean age of onset for those with the given CAG length. It is not the individual’s number of years to onset—which is unknowable—and is slightly different from the individual’s expected years to onset, given that they have reached their current age without already experiencing onset.)

A limitation of this YTO approach is that it can only approximate the relationship between true years to HD onset and the outcome measures. As noted earlier, the YTO calculations are slightly biased estimates of participants’ expected years to onset. Furthermore, a person’s true years to onset has a probability distribution around the CAG-specific average. For concave relationships, such as those we typically expect in the neurodevelopment of brain volumes, substitution of an average value for a probability distribution causes at least slight underestimation of the predicted value that would be obtained from a model based on the true (but unknowable) number of years from onset (Jensen’s inequality).

We assess the relationship between YTO and age- and sex-adjusted outcome measures in GE individuals using an additional mixed effects regression, again including random effects for repeated measures of the same participant and for similarities between participants from the same family. Similar to the GNE model described above, the potentially nonlinear influence of YTO is modeled using restricted cubic splines with degrees-of-freedom chosen by AIC. Sex and sex interactions with YTO are tested and included in the model if significant. The mixed effect models are fitted by maximum likelihood and F-test degrees of freedom are estimated using the Satterthwaite approximation. The summary of the resulting model indicates a p-value for the effect of YTO, which, if significant, indicates a statistically meaningful difference of GE from GNE along the YTO trajectory. Finally, we plot these relationships and their 95% confidence intervals to determine where these differences occur along the trajectory (50−0 YTO)

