Be diagnosed with JOHD by a trained neurologist prior to the age of 21, based on motor symptomology (the participant’s genetic status is confirmed after consent is obtained).Be between 6–30 years old at baseline. Thus, even though the diagnosis is made prior to 21, assessment for the study is not restricted to ages under 21.Not be bed-ridden, unable to communicate, or beyond travel conditions that are too strenuous for the individual.

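### Years to onset mixes CAG length with age; with no CAG term and no within-person split, the GE model cannot on its own support a conclusion about timing

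*Protocol article*

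**What the plan says.** The section on statistical analysis using YTO models defines the scale: "YTO is then calculated by simply subtracting participants’ ages (in years) from age of motor symptom onset". Onset age depends on CAG alone. GE outcomes are first corrected for age and sex with a model fitted in GNE participants. Then: "We assess the relationship between YTO and age- and sex-adjusted outcome measures in GE individuals using an additional mixed effects regression". The terms named are a YTO spline with degrees of freedom chosen by AIC, sex and sex-by-YTO if significant, and random effects for participant and family. A significant YTO term is read as a GE–GNE difference along the trajectory, and the plotted curve is used to locate it between 50 and 0 YTO.

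The power section states the central hypothesis on the same scale: larger brain volume and stronger cognition before 20 YTO, smaller and weaker from 20 to 0. The Discussion adds that replication would argue for caution about lowering huntingtin early in the disease.

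The listed limitations of YTO are that the name is a slight misnomer, that the value is slightly biased, and that averaging over a concave curve underestimates (Jensen's inequality). Confounding of YTO with CAG is not among them.

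Table 1 reports CAG relations in childhood that differ in sign. For general ability (GAI): "GAI scores increased and decreased with repeat length before and after 40–41 repeats, respectively". For the striatum: "CAG repeat length is positively correlated with early life striatal volume", with steeper later decline.

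**The concern.** Two people at different YTO can differ in age, in CAG length, or in both. If CAG length affects the level of an outcome throughout life, people with short repeats (high YTO) and long repeats (low YTO) will differ even when nobody changes relative to GNE peers. The planned model has only the YTO term to absorb that difference, so it would be drawn as movement along a trajectory.

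The conclusions at stake are about time: development first, a turn near 20 YTO, then degeneration, and an inference about how early an intervention might do harm. Those need change over time, not a difference between genotypes.

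**Working it through.** **1. Reproduce the plan's own figure.** The introduction's worked example reads: "An 8-year-old with a CAG repeat length of 48 and a 22-year-old with a CAG length of 43 both have 26 YTO". The onset formula as printed does not give this:
- CAG 48, age 8: 21.54 − (9.556 − 0.146×48) − 8 = 10.99.
- CAG 43, age 22: 21.54 − (9.556 − 0.146×43) − 22 = −3.74.

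With onset = 21.54 + exp(9.556 − 0.146×CAG):
- CAG 48, age 8: 34.32 − 8 = 26.3.
- CAG 43, age 22: 48.06 − 22 = 26.1.

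The exponential form matches the example and is used below. It is inferred from the document's own figures. Taken literally, the printed form moves onset by only 0.146 year per repeat, YTO would be almost purely age, and this point would not arise.

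**2. Reach of each CAG length at ages 6–30** (onset − 6 to onset − 30):

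| CAG | YTO at age 6 | YTO at age 30 |
|---|---|---|
| 40 | 56.6 | 32.6 |
| 42 | 46.2 | 22.2 |
| 44 | 38.5 | 14.5 |
| 50 | 25.1 | 1.1 |
| 56 | 19.5 | −4.5 |

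Each length covers 24 years, so none spans 50–0. CAG 40–42 never falls below 20 YTO, and CAG 56 or more is never above it. The two sides of the 20-YTO hypothesis therefore compare partly different genotypes.

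**3. Where YTO variance comes from.** The Participants section says: "We aim to recruit an even distribution of subjects across age groups". Taking age as uniform on 6–30 gives variance 24²/12 = 48. The article gives no CAG distribution, so six were assumed. Example: a bell shape around 44 with SD 3 gives an onset SD of 8.4, variance 70.6, and a CAG share of 70.6/(70.6 + 48) ≈ 0.59.

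Across the six, CAG supplies 43–69% and age between people 30–55%. The power section expects 400 visits from 180 GE participants, or 2.22 each. At annual spacing, within-person change supplies 0.3–0.5% of YTO variance; at three-year gaps, up to 4.0%.

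**4. Information from repeat visits.** Variance share is not information share. With annual visits, the within-person part carries 3–5% of the information on a linear slope at an intraclass correlation (ICC) of 0.80, 23–35% at 0.98 and 38–52% at 0.99. The article states no ICC.

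**5. Simulation of a fixed CAG effect.** Inputs: 180 GE people with 2–3 annual visits, and an effect of −0.10 SD per repeat (zero at CAG 43) with no change over time. The fitted model was a restricted cubic spline in YTO, 1–5 df by AIC, with a subject intercept. There were 400 runs per setting, over ICC 0.80–0.98.

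| Assumed CAG | YTO p < 0.05, planned model | With CAG and CAG² added |
|---|---|---|
| Mean 43, SD 2 | 36–52% | 3.7–6.5% |
| Mean 44, SD 3 | 61–82% | 4.0–6.0% |
| Uniform 40–50 | 87–95% | 4.0–6.8% |

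The mean fitted curve runs from +0.03 to +0.12 SD at 40 YTO down to −0.20 to −0.52 SD at 10 YTO. With −0.05 SD per repeat, rejection is 30–33%. With no CAG effect it is 9–11%, because AIC picks the spline, so not all of the excess over 5% is confounding.

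A linear-YTO version avoids that selection. At ICC 0.98 with annual visits it rejects in 30%, 60% and 86% of runs for CAG mean/SD of 43/2, 44/3 and 45/4, against 3–7% with the CAG terms.

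**6. Opposite sign.** With +0.10 SD per repeat, the artefact is about +0.4 to +0.7 SD at 0–10 YTO and −0.16 to −0.18 SD at 40–50 YTO. That is the reverse of the hypothesis.

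**The case against.** Several counterarguments have force.

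- A reader might infer that the YTO curve is almost entirely a comparison between CAG lengths. It is not. The curve is almost entirely between persons, but age differences at the same CAG supply 30–55% of YTO variance and carry cross-sectional information about time.
- A reader might infer that the bias favours the hypothesis for brain volume, the primary outcome. The document does not establish that. It reports a positive CAG relation for early striatal volume, greater brain volume with higher repeats, and cortical volume unaffected by CAG. Only the GAI result beyond 40–41 repeats points the hypothesised way, and GAI is a secondary outcome. The text also places the cognitive peak at 43 repeats and attributes later decline at longer repeats to degeneration, which is a stage effect.
- A reader might infer that repeat visits give no protection. For highly repeatable measures they carry real weight, which dilutes the artefact without removing it.
- A significant YTO term is not a false finding on the plan's literal reading. A fixed CAG effect among GE participants is a real difference from GNE.
- CAG effects are a stated aim, and an unseen analysis plan may hold a CAG-adjusted model. But the article spells out the GE model and its reading, and a general aim to study CAG does not change either.
- Adding CAG as linear plus quadratic terms makes linear YTO nearly minus age, close to the age-plus-CAG modelling the authors deliberately left. This is a good reason not to replace the planned model.

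**Conclusion.** The concern holds as a limit on interpretation. As specified, the GE model cannot separate a fixed CAG effect on level from change over time. It may mimic the hypothesised pattern for some outcomes and mask or reverse it for others. The YTO test remains usable as evidence that GE differs from GNE. It is not sufficient alone for a transition near 20 YTO or for the Discussion's caution about early intervention.

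The size rests on assumptions: the CAG distribution, ICC, visit spacing, and fixed effects of 0.05–0.10 SD per repeat, none of which the article gives. The simulations omit family effects and treat the ICC as known. The reach of each CAG length needs only the 6–30 age range and the exponential onset form.

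**What to change.** Keep the YTO spline model as the planned test and the basis of the power calculation. Beside it, pre-specify:

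1. The same GE model with CAG added (linear plus quadratic, or a 2-df spline), with curves drawn for given CAG lengths only over the YTO range each one covers.
2. A split of YTO into the person's mean and the deviation from it, reporting the within-person slope.

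State that wording about trajectory, inflection or transition depends on agreement with both. Add CAG–YTO confounding to the limitations. Reconcile the printed onset formula with the 26-YTO example.

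Cost: no new data, since CAG is measured for every participant. The YTO standard error in the adjusted model rises about 1.15- to 1.6-fold, so Table 5 does not apply to it. Dividing the projected non-centrality by 1.15² = 1.32 to 1.6² = 2.56, at alpha 0.01 and for the same YTO coefficient, lowers power for cortical gray matter from 0.995 to about 0.97–0.73, and for GAI from 0.997 to about 0.98–0.78. The companion analyses should therefore be judged on estimates and intervals, and a non-significant adjusted result should not be read as absence of change.

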To assess the relationship between age- and sex-adjusted neuroimaging variables (e.g., cortical grey and white matter volume, striatal volume, corticostriatal structural and functional connectivity, etc.) and clinical outcomes in GE individuals, we apply modeling techniques as described above. The models include random effects of subject and family, but exclude age and sex, as the values will have already been corrected using the data from GNE participants. Imaging measures are generally predictor variables, and clinical measures are the outcomes, reflecting the potential causal relationships between the two measurement classes. As in our previous work [17], we also split our GE participants into two groups with a cutoff of 20 YTO and test for differences in the imaging versus clinical relationships. This is based empirically on our work [17] showing divergence in neural and behavioral measures at this point in the YTO trajectory and because of work showing an upward trend in NfL at 20 YTO [18]. As described above, potential non-linear relationships between biomarkers and clinical measures are interrogated using restricted cubic splines (up to five degrees of freedom). For all analyses, a *p* value of < 0.05 is considered statistically significant.

In addition to our hypothesis-driven analyses, we also plan to perform detailed exploratory analyses to uncover novel neuroimaging biomarkers that both distinguish GE and GNE individuals and individuals with variations in HD-related single nucleotide polymorphisms (SNPs). For example, machine learning approaches, such as deep learning, have been applied to neuroimaging data from patients with neurodegenerative disorders to identify how those SNPs affect brain anatomy and function [81]. As mentioned above, SNPs in several genes explain variation in the eventual onset of motor symptoms in HD [32–34]. Using deep learning and other machine learning approaches as exploratory tools may reveal new mechanistic information about how these SNPs shape neurodevelopment and -degeneration.

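### Final F-tests and 95% intervals are taken from maximum-likelihood fits, which make standard errors slightly too small: minor for the main YTO model, possibly more for the 20-YTO split

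*Protocol article*

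**What the plan says.** All of this stands in the protocol article under Statistical analysis using YTO Models.

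- **Estimation.** "The mixed effect models are fitted by maximum likelihood and F-test degrees of freedom are estimated using the Satterthwaite approximation". No refit by REML is mentioned.
- **Main test.** "The summary of the resulting model indicates a p-value for the effect of YTO", and a significant result is read as a difference between gene-expanded (GE) and gene-non-expanded (GNE) participants.
- **Location of the difference.** The authors write that "we plot these relationships and their 95% confidence intervals to determine where these differences occur along the trajectory", over 50 to 0 YTO.
- **Spline terms.** The YTO effect is "modeled using restricted cubic splines with degrees-of-freedom chosen by AIC". The ceiling is five degrees of freedom, and near-ties in AIC go to the simpler model.
- **Imaging-clinical models.** These reuse the same techniques, again with up to five spline degrees of freedom. Here the authors add that "we also split our GE participants into two groups with a cutoff of 20 YTO" and test whether the imaging-clinical relationships differ. Neither the group sizes nor the form of that test is given.
- **Threshold.** For all analyses a p "value of < 0.05 is considered statistically significant".

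**The concern.** AIC comparison of models with different fixed effects needs ML, so that part of the plan is sound. The difficulty comes at the next step, because the only fit named for the final F-tests and intervals is the same ML fit. ML variance components take no account of the degrees of freedom spent on fixed effects, so they are biased downward. Satterthwaite degrees of freedom change the reference distribution but do not correct the underestimated variance. F statistics are therefore somewhat too large and intervals somewhat too narrow.

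The bias grows with the number of fixed-effect terms relative to the number of participants. The analysis most exposed is therefore the 20-YTO split with flexible splines, where the nominal 5% test could run above 5%. The whole-GE trajectory model is much less exposed.

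**Working it through.** **Inputs from the article.** 180 GE participants with about 400 visits, and a Kids-HD base of 79 GE participants (Power analysis and sample size calculation); up to five spline degrees of freedom; alpha 0.05 for the analyses and 0.01 for the power table.

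**Assumptions (not in the article).** Participant-plus-family share of variance 0.90 (sensitivity 0.50); about 1.3-1.4 GE participants per family; a below-20-YTO group of 20 to 90.

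**1. The plan's own figures.** Projected F = 2.28 × Kids-HD F, and NCP = (F − 2F/ddf − 1) × ndf, with ddf scaled by 2.278. For PANESS, 8.92 × 2.28 = 20.34 and NCP = 18.95 (Table 5: 18.933); power at 0.01 is 0.956, as stated. Thalamus gives 0.916 and cortical thickness 0.406, also as stated.

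**2. Effect on Table 5.** Shrink each Kids-HD F by 1 − p/79, with p = ndf + 1. For thalamus, 1 − 2/79 = 0.975 and power goes from 0.916 to 0.908. PANESS goes from 0.956 to 0.951 and cortical thickness from 0.406 to 0.393. The largest change is 1.3 points. The claim of at least 90% power, from which the article exempts cortical thickness, stands.

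**3. Simulation.** 2,000 runs per row with no YTO effect, random intercepts for participant within family, fixed spline df, and Satterthwaite F-tests. The same data were fitted by ML and by REML. Monte Carlo error on the type I rates is about 0.005-0.008.

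| Participants, spline df | SE ratio ML/REML | Type I error ML → REML | Band coverage ML → REML |
|---|---|---|---|
| 180, 5 df | 0.990 | 6.8% → 6.3% | 94.2% → 94.4% |
| 180, 5 df plus sex-by-spline | 0.980 | 6.6% → 6.2% | 94.1% → 94.6% |
| 90, 5 df | 0.984 | 6.5% → 5.5% | 94.5% → 94.9% |
| 60, 5 df | 0.976 | 7.9% → 6.3% | 94.1% → 94.7% |
| 45, 5 df | 0.968 | 7.5% → 5.6% | 93.6% → 94.5% |
| 30, 5 df | 0.952 | 10.7% → 7.7% | 92.9% → 94.3% |
| 30, 5 df, variance share 0.50 | 0.935 | 13.5% → 8.1% | 91.7% → 93.8% |
| 30, 1 df | 0.969 | 7.2% → 6.8% | 93.8% → 94.7% |
| 20, 5 df | 0.926 | 14.1% → 8.3% | 92.0% → 94.4% |

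A separate simulation gave SE ratios of 0.992, 0.976 and 0.951 at 180, 60 and 30 participants with five df, in agreement.

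**4. The split as one pooled model.** Use the between-participant approximation F_ML = F_REML × n/(n − p), so type I error = P{F(k, n − p) > F₀.₉₅(k, n) × (n − p)/n}. With a group-by-spline interaction, p = 2(k + 1). At n = 180:

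- k = 1, p = 4: 5.3%
- k = 3, p = 8: 5.8%
- k = 5, p = 12: 6.6%

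This shortcut overstates the SE shortfall. At five df, √(1 − p/n) with p = 6 implies 10.6%, 5.1% and 1.7% short at 30, 60 and 180 participants. The simulation gives 4.8%, 2.4% and 1.0%.

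**5. Could the below-20-YTO group be small?** Under Lessons from Kids-HD, a 22-year-old with 43 repeats is placed at 26 YTO. That implies onset at 48, so such a person drops below 20 YTO only after age 28. An 8-year-old with 48 repeats, also at 26 YTO, does so after age 14. With enrolment ending at 30 and half the sample aged 6-18, a small group is plausible, but its size cannot be derived from the article.

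**The case against.** The strongest defence is that ML is a disclosed, asymptotically valid method that matches both the AIC step and the power calculation, and that at 180 participants the choice hardly matters. For the main YTO model that stands.

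Three stronger readings are tempting and not supported.

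- **That the trajectory bands are materially too narrow and enlarge the region where GE and GNE are said to differ.** Those bands come from the model of all eligible GE participants. The 20-YTO split belongs to the imaging-clinical analysis, where no bands are mentioned. The coverage loss from ML in the whole-GE model is about 0.2 points (about 0.5 with sex-by-spline terms).
- **That near-onset tests run at 11% or more.** This needs separate fits, a small group and five spline terms together. The article establishes none of these. Testing whether relationships differ is most naturally an interaction in one model. Five terms is a ceiling under AIC selection: in Table 5, for the YTO models, 7 of 15 rows have ndf 1 and only striatum and globus pallidus have 5.
- **That REML alone restores 5%.** It does not in the smallest groups simulated, so part of the excess there has other causes.

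None of this removes the narrower point: the article commits to ML for final inference, and the bias has a known direction and a simple remedy.

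**Conclusion.** The point holds as a minor improvement.

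- **Whole-GE YTO model.** Standard errors are about 1-2% short, type I error rises by less than one point, and Table 5 is essentially unaffected.
- **20-YTO split, pooled model.** Type I error is about 5.3-6.6% for 1-5 spline df.
- **20-YTO split, separate fits.** With 30-60 participants below 20 YTO and five df, standard errors are about 2-5% short and type I error is roughly 5.5-11%, depending on the df method and assumptions. The simulation above gives 7.5-10.7% under its main variance assumption and 13.5% at 30 participants with the lower variance share. With one spline df, moving to REML changes little.

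The separate-fit figures rest on assumed group sizes, family structure and variance shares. The simulation fixed the spline df, so uncertainty from AIC selection and from the GNE-based age and sex correction is not included.

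**What to change.** Keep ML for choosing the spline degrees of freedom by AIC. Then refit the selected model by REML and take the F-tests, the Satterthwaite or Kenward-Roger degrees of freedom, and the 95% intervals from the REML fit. Apply this to the whole-GE YTO models and to the imaging-clinical models. State whether the 20-YTO comparison is an interaction in one model or two separate fits. If the fits are separate, limit the spline terms in the smaller group, since REML reduces the excess error but may not remove it there.

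The cost is one extra refit per model and slightly wider intervals. Data collection and sample size do not change.
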